3.4 Secondary Endpoints

1. COVID-19 severity grading according to WHO Clinical Progression Scale (scores 1–10).

2. Overall survival rate at 12 months post-transplant.

3. Time to first COVID-19 diagnosis (days from transplantation to first positive test).

4. Quantitative or semiquantitative SARS-CoV-2 antibody titers measured at predefined intervals (baseline, pre-infusion, and 14, 28, 60, 90, 180, and 365 days post-transplant).

5. Number and proportion of adverse events (AEs) and serious adverse events (SAEs) related to plasma infusion, graded according to CTCAE v5.0.

6. Association between CCP antibody titer and risk reduction for COVID-19 infection or severe disease.

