3.2 Secondary Objectives

1. To assess the severity and clinical course of COVID-19 infection (mild, moderate, severe, or critical) in CCP versus control groups.

2. To evaluate overall survival (OS) at one year post-transplant.

3. To determine the time to first SARS-CoV-2 infection after transplantation.

4. To assess the kinetics and durability of anti–SARS-CoV-2 antibody levels following CCP infusion.

5. To evaluate the safety and tolerability of CCP administration by recording infusion-related and systemic adverse events.

6. To explore correlations between antibody titers and clinical outcomes.

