**Ⅴ. Statistical Considerations**

5.1 Sample Size Determination

The sample size was calculated based on the expected difference in the incidence of COVID-19 infection between the CCP group and the control group.

According to preliminary clinical observations and published data, the infection rate within one year after HSCT was estimated at 80% in the control group and 50% in the CCP group.

Assuming a two-sided significance level (α = 0.05) and a statistical power of (1 – β = 0.80), and using a log-rank test for comparison between groups, the required total sample size was calculated to be 72 participants (36 per group).

This number also accounts for an estimated 10% attrition rate due to loss to follow-up or early withdrawal.

The sample-size calculation was performed using PASS software version 15.0 (NCSS, Kaysville, UT, USA).

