5.3 Statistical Methods

1. Descriptive Statistics:

Continuous variables will be summarized as mean ± standard deviation (SD) or median (interquartile range, IQR) as appropriate.

Categorical variables will be summarized as counts and percentages.

2. Group Comparisons:

Continuous variables: Student’st-test (normally distributed) or Mann–WhitneyU test (non-normally distributed).

Categorical variables: Chi-square (χ²) or Fisher’s exact test.

Time-to-event data (e.g., infection-free survival): Kaplan–Meier analysis and log-rank test.

3. Multivariate Analysis:

Cox proportional-hazards regression will be used to identify independent factors associated with infection risk or survival.

Variables withP < 0.10 in univariate analysis will be included in the multivariate model.

4. Confidence Intervals:

Two-sided P values < 0.05 will be considered statistically significant.

For all main comparisons, 95% confidence intervals (CIs) will be reported alongside P values.

5. Correction for Multiple Comparisons:

When multiple secondary endpoints are analyzed,P values will be adjusted using the Benjamini–Hochberg false discovery rate (FDR) method to control for type I error.

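### Titres to day 365 are read as antibody durability after CCP and correlated with outcomes without separating post-infection samples; at day 365 they cannot show CCP durability

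*Protocol*

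**What the plan says.** - **Sampling.** Secondary endpoint 4 (Protocol, 3.4) lists titres at baseline, pre-infusion and "14, 28, 60, 90, 180, and 365 days post-transplant". The visit table in 4.7 collects them at 6 and 12 months.
- **Use as durability.** Objective 4 in 3.2 is "To assess the kinetics and durability of anti–SARS-CoV-2 antibody levels following CCP infusion".
- **Use as a correlate.** Objective 6 in 3.2 is "To explore correlations between antibody titers and clinical outcomes". Endpoint 6 in 3.4 is "Association between CCP antibody titer and risk reduction for COVID-19 infection or severe disease".
- **Tests.** Section 5.3 has only a generic rule for continuous variables: Student's t or Mann–Whitney.
- **Expected infections.** Section 5.1 states: "infection rate within one year after HSCT was estimated at 80% in the control group and 50% in the CCP group".
- **Passive antibody.** Section 2.3 gives an IgG half-life of about 21 days. Figure 1 puts the infusions at days 14, 28, 60 and 90.

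No section excludes, stratifies or flags titres taken after infection or vaccination. The one censoring rule (5.4) concerns participants who withdraw before infection assessment.

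**The concern.** A recipient's titre has at least two sources in this trial: antibody passed on by the plasma and antibody made after infection. Objective 4 treats the whole series to day 365 as information about the first. By the protocol's own figures, the passive part is almost gone at the end of follow-up while infection is common, and more common in controls. If CCP works, more controls are infected and more of them carry antibody of their own, so CCP's apparent durability looks worse the better it protects.

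Objective 6 has a related problem. Infection is the primary endpoint and also a cause of high titre. Unless the titre must precede the outcome, a positive association between antibody and infection can appear simply because infection raised the antibody.

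**Working it through.** **The planning figure.** The infection rates used below come from the sample-size section, so that calculation was checked first. The hazard ratio is ln 0.5 / ln 0.2 = 0.431. With two-sided α = 0.05 and power 0.80, Schoenfeld's formula gives 4 × (1.960 + 0.842)² / (ln 0.431)² = 44.2 events. Treat 10% attrition as exponential censoring over the year, with δ = −ln 0.9. The event probability λ/(λ+δ) × (1 − exp(−(λ+δ))) is then 0.770 for control (λ = 1.609) and 0.477 for CCP (λ = 0.693), mean 0.6235. So N = 44.24 / 0.6235 = 71.0, or 36 per arm. The stated 72 is reproduced.

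**Passive antibody left.** In units of one infusion's increment, P(t) = Σ 2^(−(t − d)/21) over d = 14, 28, 60, 90.
- Day 180: 0.0042 + 0.0066 + 0.0190 + 0.0513 = 0.081.
- Day 365: 0.00018, or about 0.02%. The last infusion is then 275 / 21 = 13.1 half-lives past.

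**Share infected.** With constant hazards matched to 80% and 50% at day 365 (an assumption for earlier days), the shares are 1 − 0.2^(t/365) and 1 − 0.5^(t/365).
- Day 180: 0.548 × 36 = 19.7 controls and 0.290 × 36 = 10.4 CCP.
- Day 365: 28.8 and 18.0.

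**Difference in arm means.** Let R be the mean titre contributed by infection in someone ever infected, in increments. R is not in the protocol, so it is left free. It is taken as equal in both arms, and background antibody from recovery or vaccination is assumed equal, so it cancels. Then

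CCP − control = P(t) − (share infected in control − share infected in CCP) × R.

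| Day | P(t) | Control infected | CCP infected | Difference | R at which means reverse |
|---|---|---|---|---|---|
| 90 (just after infusion) | 1.582 | 0.328 | 0.157 | 0.170 | 9.3 |
| 180 | 0.081 | 0.548 | 0.290 | 0.258 | 0.31 |
| 365 | 0.00018 | 0.800 | 0.500 | 0.300 | 0.0006 |

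For half-lives of 14 to 28 days, the day-180 break-even runs from 0.06 to 0.77. The day-365 value is still only about 0.007 at 28 days.

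**Ranks.** A Mann–Whitney simulation used 36 per arm and R = 0.25 to 5, with an assumed lognormal spread and a low background.
- Day 90: CCP significantly higher in 98–100% of trials.
- Day 180: controls ranked higher in only 2–37%.
- Day 365: controls ranked higher in about 98–99%, significantly so in about 56–60%; CCP never significantly higher.

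**The case against.** **No arm comparison of titres is named.** Objective 4 concerns levels after CCP infusion, which only one arm receives, so a within-arm description is a natural reading. This stands: the between-arm test is only implied by the generic rule in 5.3. It does not rescue day 365, because within the CCP arm alone half the participants are expected to be infected and 0.02% of an increment remains.

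**Handling of post-infection samples is often left to the SAP, which is not shown.** This has force as to technique. But the protocol itself designates titres to day 365 as evidence of durability after CCP, and that target cannot be met there on its own figures. For the same reason, replacing t-tests with a mixed model would be a preference, and it is not asked for here.

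**Day 180 is not shown to reverse.** This stands. A reader might infer reversal at R above 0.22 from 0.548R > 0.290R + 0.710 × 0.081, but that gives infected CCP participants no passive remainder. Keeping it gives 0.081 / 0.258 = 0.31, and ranks usually do not reverse.

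**A reader might infer that most late samples follow infection.** That is not so at day 180, where (19.7 + 10.4) / 72 = 42%. Nor is it so in the CCP arm, with 29% at day 180 and 50% at day 365.

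**Endpoint 6 in 3.4 may mean the titre of the infused plasma.** Section 4.4.1 sets a titre criterion for each unit, and a recipient's infection cannot change it. The cause-and-effect point therefore rests on objective 6 in 3.2, which is exploratory in wording.

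**Recipients may respond weakly to infection.** Sections 2.1 and 2.2 describe poor humoral responses early after transplant. The day-365 break-even is so small that this hardly matters there.

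**Conclusion.** The point holds for two uses of the titres.

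First, day-365 titres cannot show CCP durability. This follows from the protocol's infection rates, infusion days and half-life. Any comparison of arm means there would favour controls for almost any response to infection (R above about 0.0006), given equal R and equal background in the two arms. Day 180 is a mixture: about 20 vs 10 infected, 8% of an increment left, and a direction that depends on an unknown R around a break-even of 0.31 (0.06 to 0.77). It should be called confounded, not wrong. Day 90 is sound for R up to about 9 just after the fourth infusion.

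Second, correlating titres with infection under objective 6 in 3.2 is circular unless the titre precedes the outcome.

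The protocol does not support the broader inference that the whole titre series is uninformative. Figure 1 places weekly antibody sampling up to day 120, where passive antibody is measurable. Only secondary objectives are affected; the primary endpoint and N = 72 are not.

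**What to change.** - **3.2(4) and 3.4(4).** Base the CCP kinetics and durability analysis on samples taken before the first recorded positive SARS-CoV-2 test, and before post-transplant vaccination where that date is recorded. Report later samples separately by infection status.
- **3.2(6).** Relate outcomes only to titres measured before the outcome, for example the latest pre-infection titre as a time-varying covariate in the Cox model.
- **3.4(6).** State whether the titre is that of the plasma product or of the recipient, and apply the same rule only if the recipient's is meant.

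**Cost.** The infection cut needs wording only, since 3.4(3) already records time to the first positive test. The vaccination cut is conditional because 4.5 and 4.7 list no vaccination data. Late samples become fewer: about 16 controls and 26 CCP participants at day 180 (36 − 19.7 and 36 − 10.4), and 7 and 18 at day 365, before deaths and withdrawals. Those left are a selected uninfected group; if titre protects, low-titre participants leave first and durability can look better than it is. Some will have had undetected infections, because 4.7 schedules no PCR at 6 or 12 months and the twice-weekly testing in Figure 1 ends at day 120. Late results therefore need cautious description even after the change.

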**Secondary Endpoints:**

1. Incidence and severity of COVID-19 (mild/moderate/severe).
2. Overall survival (OS) at one year.
3. Time to first SARS-CoV-2 infection.
4. Incidence of adverse events related to plasma infusion.
5. SARS-CoV-2 antibody titers and their kinetics over time.

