4.3 Blinding

This is an open-label study; neither investigators nor participants are blinded to treatment allocation.

However, laboratory personnel responsible for SARS-CoV-2 testing and antibody titer quantification are blinded to treatment assignment to minimize analytical bias. Clinical investigators and patients were aware of group assignment solely for safety monitoring and transfusion logistics.

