4.4.2 Control Group

Participants in the control arm receive standard supportive care according to institutional post-HSCT guidelines, without plasma infusion.

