4.6 Safety Monitoring

All adverse events (AEs) and serious adverse events (SAEs) occurring during or after CCP infusion will be recorded.

Events are graded according to Common Terminology Criteria for Adverse Events (CTCAE) version 5.0, categorized by severity (Grade 1–5) and relationship to the study intervention (definite, probable, possible, unrelated).

All SAEs are reported within 24 hours to the principal investigator and reviewed by the institutional ethics committee.

An independent Data and Safety Monitoring Board (DSMB) oversees trial conduct and safety data.

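### The only adverse-event endpoint counts events attributed to plasma, so it cannot compare non-fatal harm between the randomised arms, although the safety objective is wider

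*Protocol*

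**What the plan says.** The adverse-event endpoint is item 5 of Protocol section 3.4: "Number and proportion of adverse events (AEs) and serious adverse events (SAEs) related to plasma infusion, graded according to CTCAE v5.0". The Study Summary lists the same restriction: "Incidence of adverse events related to plasma infusion". Neither endpoint list, nor the exploratory list in section 3.5, contains another adverse-event endpoint.

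The objective that it serves, item 5 of section 3.2, is wider: "To evaluate the safety and tolerability of CCP administration by recording infusion-related and systemic adverse events".

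Other sections bear on the point:

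- Section 4.4.2: controls receive "standard supportive care according to institutional post-HSCT guidelines, without plasma infusion". No sham infusion is described.
- Section 4.3: "This is an open-label study; neither investigators nor participants are blinded to treatment allocation". Only the laboratory staff who test for virus and antibody are described as blinded.
- Section 4.6: each event is categorised by "relationship to the study intervention (definite, probable, possible, unrelated"). The recording rule there is tied to the period during or after a plasma infusion.
- Section 5.2: the safety population includes control participants.
- Section 4.1: participants are followed for safety events throughout observation.
- Study Summary, Safety Monitoring: events are summarised by severity and relationship. Arm is not mentioned.

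**The concern.** The endpoint is narrower than its objective, and what it drops is what a randomised control arm is there to measure. Recipients of an allogeneic transplant have many background complications, so deciding for a single patient whether an event came from plasma or from the transplant is hard. Comparing all events by randomised arm avoids that judgement. An endpoint limited to attributed events depends on it entirely.

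The judgement can err in both directions. Harm from plasma that looks like a transplant complication, and is labelled unrelated, adds nothing to the endpoint. A background event labelled possibly related after an infusion counts towards the plasma arm, with no matching count in controls. At stake is whether the trial can say anything from its randomised comparison about non-fatal harm, which is half of its stated efficacy-and-safety purpose (section 4.1).

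**Working it through.** The protocol gives no safety rate, safety power or safety sample size, so there is no stated figure to reproduce. The main result follows from the definitions. The arithmetic only illustrates its size.

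**Step 1. Objective against endpoint.** The objective calls for "recording infusion-related and systemic adverse events". The endpoint keeps only the events related to plasma infusion. Systemic events judged unrelated fall within the objective and outside the endpoint.

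**Step 2. What controls can contribute.** No plasma is given in the control arm, so no event there can be related to a plasma infusion. With 36 per arm (section 5.1) the control count is 0/36 whatever happens to those patients. Complete recording of events in controls would not change this. No assumption is needed.

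**Step 3. How much real harm the endpoint could miss (assumed figures).** Suppose plasma raised the share of participants with at least one serious event from 40% to 60%, a true excess of 20 points. If a fraction *f* of that excess is labelled related, the endpoint shows 0.20 × *f*:

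- *f* = 0.10: 0.20 × 0.10 = 2 points
- *f* = 0.50: 0.20 × 0.50 = 10 points

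In either case the control figure is 0%.

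**Step 4. What would happen if the attributed count were tested between arms.** The protocol does not say that it will be, so this step is conditional. Two-sided Fisher exact P for *k*/36 against 0/36:

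| *k* | P |
| --- | --- |
| 5 | 0.054 |
| 6 | 0.025 |
| 7 | 0.011 |
| 8 | 0.005 |

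Suppose plasma is harmless, but a share *p* of plasma-arm participants have a background event labelled related (assumed range). The number so labelled is Binomial(36, *p*). An unadjusted P < 0.05 needs at least 6.

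Section 5.3 adjusts secondary-endpoint P values by Benjamini–Hochberg. If the six endpoints in section 3.4 gave one P value each and no other were small, the threshold would be 0.05/6 = 0.0083, which needs at least 8.

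| *p* | Chance of at least 6 (unadjusted) | Chance of at least 8 (adjusted, six tests) |
| --- | --- | --- |
| 10% | 15% | 2% |
| 15% | 46% | 16% |
| 20% | 75% | 43% |

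For contrast, when events are counted irrespective of cause and true rates are equal in the two arms (assumed 30% to 90%), Fisher's test at 36 per arm is significant at an unadjusted 0.05 in 1.4% to 2.8% of trials.

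**Step 5. Precision of the repaired comparison.** With both proportions near 50%, the 95% confidence interval half-width is 1.96 × √(2 × 0.25/36) = 0.231, about 23 points.

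**The case against.** The strongest reply is that an endpoint of plasma-related events is simply a tolerability rate for the plasma arm, and a legitimate one. No section says that it will be compared between arms. Section 5.3 lists tests by type of variable, and the tabulation of adverse events is commonly left to the analysis plan. That stands. A reader might infer that the protocol plans a significance test against a guaranteed zero, with a false-alarm chance of 15% to 75%. The documents do not support that: the test is not specified, and those chances also ignore the Benjamini–Hochberg rule. Step 4 shows only what would follow if the test were run.

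A second reply is that harm not attributed to plasma is not lost from the trial. This also stands in part. In the plasma arm, unrelated events are recorded and summarised (section 4.6 and the Safety Monitoring summary). The safety board reviews adverse events, infections and survival (section 5.5), and 12-month overall survival captures deaths whatever their cause. It would therefore go too far to say that the safety objective cannot be answered at all. What these provisions do not supply is an endpoint that compares non-fatal events by arm.

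Third, the protocol does not say who assigns relationship. That the assessor knows the arm is an inference, though a likely one, because "neither investigators nor participants are blinded to treatment allocation" and no blinded review of causality is described.

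Finally, the repaired comparison would be imprecise. Its half-width of about 23 points exceeds the 20-point excess assumed in step 3, and Fisher's test would detect 60% against 40% with a power of only about 29%. That is a reason to report an estimate with its interval. It is not a reason to go without the comparison.

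**Conclusion.** The point holds as a mismatch between objective and endpoint. As written, the only adverse-event endpoint cannot compare non-fatal harm between the randomised arms, because one arm is zero by definition. What it counts in the other arm depends on individual attribution in an open-label trial. This follows from the protocol's own definitions. It is not a detail left for the analysis plan, since that plan would take over the restricted endpoint.

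The size can be given only on assumptions: a 20-point excess could appear as 2 to 10 points. The figures on false signals apply only if the attributed count is tested between arms. The change should be made. The endpoint is secondary, and other provisions cover deaths and the recording of events in the plasma arm, so the fault does not threaten the trial as a whole.

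**What to change.** Three linked changes:

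1. Redefine section 3.4, item 5, and summary item 4 as the number and proportion of participants with any serious adverse event, and with any adverse event at or above a prespecified grade (for example grade 3), irrespective of attribution. Compare them by randomised arm over one common post-transplant window, with the difference in proportions and its 95% confidence interval.
2. Amend section 4.6 so that adverse events are recorded in controls over that same window. The present rule is tied to plasma infusion and does not clearly reach them, so without this change the comparison could lack control data.
3. Keep reactions attributed to plasma as a descriptive rate in the plasma arm, with no test against controls.

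The cost is slightly more than a change of wording: some added recording in controls, who are already followed for safety events under section 4.1, and one more table. The comparison will be imprecise (half-width about 23 points at 36 per arm with proportions near 50%) and should be reported as such.

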3.5 Exploratory Endpoints

Correlation of CCP antibody titers (or binding absorbance values) with humoral reconstitution kinetics (IgG, IgM, IgA recovery).

Influence of donor type (matched sibling, haploidentical, or unrelated donor) and conditioning regimen on infection risk and CCP efficacy.

Subgroup analyses by patient age, gender, and comorbidities (e.g., diabetes, cardiovascular disease).

**Ⅳ. Study Design and Methodology**

4.1 Study Design

This is a prospective, single-center, open-label, randomized controlled trial evaluating the prophylactic efficacy and safety of COVID-19 convalescent plasma (CCP) in adult patients early after allogeneic hematopoietic stem-cell transplantation (HSCT).

Eligible participants are randomized in a 1:1 ratio to receive either:

Experimental group (CCP group): Standard supportive care plus four planned CCP infusions.

Control group: Standard supportive care without CCP.

The total study duration for each participant is 12 months after transplantation. Participants will be followed for clinical outcomes, infection status, and safety events throughout the observation period.

4.2 Randomization and Allocation Concealment

Randomization is performed using a computer-generated sequence prepared by an independent statistician who is not involved in patient care.

Allocation follows a simple randomization design with a 1:1 ratio between the CCP group and the control group. The randomization sequence is stored securely by the data manager and concealed until the time of patient enrollment.

Upon confirmation of eligibility and signed informed consent, the investigator obtains the next available randomization code from the sealed allocation list. This process ensures that treatment assignment remains concealed until enrollment is finalized.

